### Eligibility criteria

We will include patients with ICD-10 diagnoses F20.x, F23, F25, F30-33, aged between 18 and 65 years, who are legally competent, without any issues in voice production, and have a German speaking proficiency of at least B2 (lower level in German would contain too little information content of linguistic utterances). Additionally, psychotherapists employed at the University Hospital Frankfurt will be included for the therapeutic conversations.

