### Participant timeline

In-patients and out-patients will regularly be screened for participation eligibility. If the eligibility criteria are met and in consultation with their treating clinicians, patients will be informed about their study and will have at least one day to consider participation and sign the informed consent. The same procedure applies for clinicians who participate in the study, while they only must consent once for the recording of therapy sessions with several patients who gave informed consent. From the time point on where patients agreed to participate, up to five of their regularly held therapy sessions will be recorded. After the therapy session, patients and therapists will fill out questionnaires about the psychopathology of the patient (approx. 5 min. for each). They are asked to fill out the questionnaire on the same day the therapy session took place. Table 1 summarizes the procedure and when the respective questionnaires are used.

**Table 1 T1:** Content for the schedule of enrollment and participation.

TIMEPOINT	Enrollment	Informed Consent	Recording and Questionnaires				
	*−t2*	*−t1*	*t1*	*t2*	*t3*	*t4*	*t5*
	Ongoing	After confirmation by clinician	At least 1 week between each participation				
			Up to five therapy sessions can be recorded per participant				
			Questionnaires have to be filled out the same day as the recording				
*Study admission*							
Eligibility screen	X	X					
Consultation with the treating clinician	X						
Informed consent		X					
*Recording of therapy session*			X	X	X	X	X
*Patient reported outcomes (PRO)*							
*Beck’s Depression Inventory (BDI-II)*			X	X	X	X	X
*DSI-SS-Scale*			X	X	X	X	X
MINI C Suicidality Scale			X				
*Demographics, Diagnoses and Concomitant Medication*			X				
*Therapist Ratings*							
*Global Assessment of Functioning (GAF)*			X	X	X	X	X
*Clinical Global Impression (CGI)*			X	X	X	X	X
*Brief Psychiatric Rating Scale (BPRS)*			X	X	X	X	X

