## Data collection and management

### Plans for assessment and collection of outcomes

The recording of the therapy sessions and the questionnaire data will be collected on the same day. An overview of all applied study instruments is depicted in Table 2. After giving the patient the study information and obtaining informed consent, audio recordings are conducted during routine medical activities. Up to five of their therapy sessions with a typical duration of 30–60 min are recorded. Audio recordings of therapeutic sessions are captured using high-quality recording equipment with carefully positioned microphones to minimize background noise and ensure clear speech capture. Recordings are made using a Tascam DR-40X audio recorder. Recordings are captured in stereo mode using the recorder's external left/right inputs. The audio is stored as uncompressed WAV files with a sampling rate of 48 kHz and a bit depth of 24 bit. The recorder input level is set to −12 dB, providing sufficient headroom to avoid clipping. Phantom power (48 V) is enabled to supply the external microphones. Audio signals are acquired using two external condenser microphones (the t.bone CC 75) with a frequency response of 20 Hz–20 kHz, corresponding to the standard human auditory range. Microphones are attached at the chest/collar area of the participants ensuring comparable distance to the mouth between the participants. Care is taken to ensure that the microphone grille did not come into contact with participants' clothing and is oriented toward the participant's head, in order to minimize clothing-rub noise and to enable more accurate recordings. These settings were chosen based on previous test runs using different setups of microphones and recording environments/parameters. We transcribed and diarized the recordings and manually evaluated the quality of these transcriptions with their corresponding audio recordings to find the best setup.

**Table 2 T2:** Overview of collected data.

Data category		Purpose of use	
Demographic data		Control of the study*’*s inclusion criteria	
Clinical data	Clinical Global Impression (CGI)	Dimensional measure of development of psychopathology	Assessment of the patient*’*s condition or psychopathology
	Clinical Global Impression of Suicide Severity (CGI-SS)		
	Global Assessment of Functioning (GAF)	Assessment of the general psychosocial functioning level	
	MiNi C Suicidality Scale (MiNi)	Assessment of suicide risk and preceded suicidality	

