Tier 1: Unimodal Baseline Analysis. We will analyze each modality independently to establish baseline predictive performance before considering fusion. For the text modality, we will conduct two-way mixed-effects logistic regression with outcomes (diagnostic classification or severity degree) regressed on the fixed effects of model size and temperature, with random intercepts for participant and session. Effect sizes will be reported as odds ratios with 95% confidence intervals. For the acoustic modality, we will conduct mixed-effects linear regression using a reduced set of the most clinically relevant acoustic features selected *a priori* based on prior literature associations with depression and suicidality, including pitch variability, energy measures, MFCC and jitter as predictors of continuously scored clinical outcomes (e.g., severity scores from standardized rating scales) (60, 61).Tier 2: Factorial Interaction Analysis for 2 × 2 Design. For text-based predictions, we will formally test the 2 × 2 factorial design using mixed-effects ANOVA to partition variance according to main effects (model size, temperature) and their interaction. Specifically, we will model primary outcome (e.g., predicted depression severity) as a function of fixed effects for model size (GPT-OSS-120B vs. 20B), temperature (0.1 vs. 0.8), and their interaction (Model Size × Temperature), with random intercepts for participants and sessions to account for the hierarchical data structure. This approach allows us to determine whether inference strategy recommendations (conservative vs. liberal temperature) can be applied consistently across model sizes, or whether optimization differs by model choice. If a significant Model Size × Temperature interaction emerges, it would suggest that clinical deployment requires model-specific tuning. Conversely, absence of interaction would support unified recommendations applicable regardless of computational constraints. We will report partial eta-squared (*η*²p) effect sizes with 95% confidence intervals for each factorial term.Tier 3: Multimodal fusion and Late-Fusion Integration. To evaluate how textual and acoustic information combine for clinical prediction, we will employ a structured late-fusion approach. For each of the four 2 × 2 factorial conditions, we will generate separate predictions from the GPT-OSS models (text modality) and from a logistic regression model trained on acoustic features (acoustic modality). We will then integrate these predictions through weighted averaging, with weights determined via cross-validation (80% training, 20% held-out validation) on a stratified subset of sessions. This approach maintains interpretability—each modality's contribution can be quantified—and avoids the architectural complexity that would introduce uncontrolled hyperparameter flexibility incompatible with pre-registration.We will quantify multimodal benefit by comparing fusion performance (AUC, sensitivity/specificity at clinically relevant decision thresholds) against the best unimodal baseline. If fusion provides incremental improvement beyond single modalities, we will use mixed-effects logistic regression with interaction terms to test whether the fusion benefit depends on model size or temperature setting. This tests the hypothesis that acoustic information provides complementary information that enhances text-based predictions uniformly, or whether certain model configurations better leverage multimodal information.

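### The acoustic models in Tiers 1 and 3 list only voice features as predictors and do not handle speaker sex or age, which can dilute or imitate a link with severity

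*Protocol article*

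**What the plan says.** All points are from the protocol article.

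- **Tier 1, acoustic modality** (Statistical methods for primary and secondary outcomes): "we will conduct mixed-effects linear regression using a reduced set of the most clinically relevant acoustic features selected" in advance from the literature, "including pitch variability, energy measures, MFCC and jitter as predictors of continuously scored clinical outcomes". The list that "including" opens contains acoustic features only.
- **Tier 3, acoustic arm** (same section): predictions come "from a logistic regression model trained on acoustic features (acoustic modality"). They are then averaged with the text predictions, using weights set by cross-validation.
- **Demographics.** Table 1 schedules "Demographics, Diagnoses and Concomitant Medication" once, at t1. Table 2 has a row "Demographic data" whose purpose begins "Control of the study" and goes on to name its inclusion criteria. No analytic use is given, whereas the rows for medical-record information and session recordings are assigned to analyses.
- **Eligibility.** Patients are "aged between 18 and 65 years", so age must be recorded. Sex or gender is not named anywhere as a collected item.
- **Fixity.** The closing paragraph of the statistical section says that the approach follows pre-registration, leaves no room for later methodological choices, and can be replicated directly by others.

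**The concern.** Voice features can differ between men and women, and across an age range of 18 to 65, for reasons unrelated to psychiatric illness. If the models ignore this, two things can happen.

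1. **Dilution.** Demographic variation in the feature acts as noise around its link with severity. This needs only a sex (or age) difference in the feature.
2. **A false link.** If severity also differs by sex in this sample, a feature with no link within either sex will correlate with severity overall.

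The random participant intercept does not solve this. It assumes that the participant effect is unrelated to the predictor, but speaker sex would be part of both. The fitted slope blends a within-person slope, which is free of sex, with a between-person slope, which is not.

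At stake is interpretation. The Objectives look for prognostic language markers, and Tier 3 treats each modality's share as measurable and asks whether sound adds to text. If the acoustic score partly encodes who is speaking, its fusion weight and any gain in AUC may partly reflect demographics. Without a demographic benchmark a reader cannot tell.

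**Working it through.** **The plan's own figure.** The article states no figure for the acoustic models. Its only sample-size figure, n = 162, belongs to an exact two-sided binomial test against 0.5 with g = 0.11. It reproduces: critical values 68 and 94, alpha 0.04917, power 0.80468. It contains no acoustic term, so this point does not change it.

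**Inputs.** From the article: two-sided alpha 0.05; up to five sessions per participant; a sample size counted in interviews. Assumed, because the documents give none of them: a 50:50 sex split; a sex difference dx in the feature and dy in severity, both in within-sex SDs; ICC 0.5 for feature and outcome. Age was not quantified; the mechanism is the same.

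**Step 1, closed form for one feature.** With q = p(1 − p) = 0.25 and within-sex correlation r,

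r_overall = (r + q·dx·dy) / √[(1 + q·dx²)(1 + q·dy²)].

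- Dilution, r = 0.20, dx = 2, dy = 0: 0.20/√2 = 0.141.
- False link, r = 0, dx = 2, dy = 0.3: 0.15/√(2 × 1.0225) = 0.105.
- Small feature difference, dx = 0.5: the diluted value is 0.20/√1.0625 = 0.194, and the false correlation is 0.0375/√(1.0625 × 1.0225) = 0.036.
- dx = 0 removes the effect. dy = 0 leaves dilution only.

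**Step 2, mixed model with clustering.** Simulation of a linear mixed model with a random participant intercept and dx = 2, with and without sex as a fixed effect. The designs were 40 participants × 4 sessions (160) and 54 × 3 (162), with 300 runs per cell.

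| True slope | dy | Without sex: slope | Without sex: rejected | With sex: slope | With sex: rejected |
|---|---|---|---|---|---|
| 0.20 | 0 | 0.14-0.15 | 53-61% | 0.20-0.21 | 72% |
| 0.20 | −0.5 | 0.06-0.09 | 14-24% | 0.20-0.21 | 71-72% |
| 0 | 0.3 | 0.04-0.05 | 12-13% | about 0 | 6-7% |
| 0 | 0.5 | 0.07-0.09 | 18-22% | about 0 | 5% |

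The Monte Carlo standard error at 12% is √(0.12 × 0.88/300) = 1.9 percentage points, so the third row is approximate.

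**Step 3, several features together.** The plan enters several features jointly, and other sex-related features partly stand in for sex. With independent participants, dx = 2, dy = 0.3 and no true link, a single feature is rejected in 15% (n = 80) to 26% (n = 162) of studies. Adding three features that differ by 1 SD lowers this to 9% and 13%. If all four differ by 2 SD, it is about 7% at both sizes.

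**The case against.** **The article is silent rather than wrong.** Covariate lists and normalisation often sit in a full protocol or analysis plan, and the article refers to a full protocol. The feature list is also illustrative. This has weight, and it means one cannot say that sex and age are excluded. It does not dispose of the point. The article writes out both models, down to random effects, feature-set version, collinearity limits and transformations, and claims to leave no later flexibility. Followed as written, it leaves speaker sex and age unhandled.

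**Table 2 is an overview.** A reader might infer from it that demographic covariates are ruled out. The documents do not support that: the entry is a short label in a list of collected data, not an analysis rule. It shows only that no analytic use has been stated.

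**Sex may not be on file.** A reader might take both variables as collected. Only age is certain; sex is presumed from the word demographics.

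**The size is assumed.** The 2-SD difference has no source in the documents, and the article names pitch variability, not mean pitch. This stands. At 0.5 SD the single-feature false-rejection rate is only 6-7%, and joint entry of features reduces the problem further.

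**Tier 1 aims at prediction.** A feature that predicts partly through sex still predicts. True, so the harm falls on reading features as severity markers and on the claimed acoustic contribution to fusion.

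**Covariates in the Tier 3 acoustic arm would credit demographic prediction to voice.** This is correct, and the fix avoids it.

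**Conclusion.** The point holds in a limited form. Both acoustic models are specified by acoustic features alone, no handling of speaker sex or age is stated, and the claim of a fixed analysis makes this worth settling now. The mechanism is sound, and a participant intercept does not remove it.

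Under the assumptions above (2-SD feature difference, 50:50 split, ICC 0.5, one feature), a true slope of 0.20 shrinks to 0.14-0.15 and power falls from 72% to 53-61%. A null feature is rejected in 12-13% of studies if severity differs by 0.3 SD. These figures illustrate the mechanism and do not estimate what this study will show: the effect is small if the feature differs by only 0.5 SD or if other sex-related features are in the same model. A false link further requires that severity differ by sex in this sample.

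A reader might apply the 26% rejection rate to this study. That figure treats 162 as independent people, whereas the article counts interviews, with up to five per patient.

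**What to change.** 1. Confirm that sex is recorded among the demographics at t1.
2. **Tier 1:** add sex and age as fixed effects in the acoustic mixed-effects regression.
3. **Tier 3:** keep the acoustic arm purely acoustic. Standardise its features within sex, with means and SDs estimated in the training data only.
4. Report a sex-and-age-only model as the benchmark that the acoustic and fusion models must beat. In Tier 3 this is also the safeguard for age.
5. Amend the purpose of demographic data in Table 2 to include these uses.

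The cost is two degrees of freedom in Tier 1, one small extra model and a few sentences of text. If sex is recorded, no new data are needed. The sample size does not change.

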
## Statistical methods

### Statistical methods for primary and secondary outcomes

We will employ a zero-shot prompting approach with OpenAI's recently released GPT-OSS (Generative Pretrained Transformer—Open Source Software) series models, which are available under the permissive Apache 2.0 license and have demonstrated strong performance on reasoning tasks relevant to clinical assessment. We have selected these models for several methodological and practical reasons:

First, their open-weight nature ensures full transparency and reproducibility of our analyses. Second, their mixture-of-experts architecture enables efficient deployment on clinical infrastructure with limited computational resources. Third, their documented performance on complex reasoning tasks, including healthcare-related queries, makes them well-suited for psychiatric assessment applications.

Our primary analytical comparison will involve two model sizes from the GPT-OSS family: GPT-OSS-120B (116.8 billion total parameters with 5.1 billion active parameters per token) and GPT-OSS-20B (20.9 billion total parameters with 3.6 billion active parameters per token) (58). This comparison directly addresses a critical question for clinical deployment: whether larger, more capable models provide sufficient performance advantages to justify their greater computational demands, or whether smaller, more efficient models can achieve comparable diagnostic accuracy. The GPT-OSS-120B model has been shown to achieve near-parity with state-of-the-art reasoning models on standard benchmarks while running efficiently on a single 80GB GPU, whereas GPT-OSS-20B delivers comparable performance to advanced compact models while requiring only 16GB of memory, making it feasible for deployment on standard clinical workstations or even edge devices.

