For each model size, we will systematically evaluate two distinct inference configurations defined by the temperature hyperparameter, which controls the randomness of model outputs. We will test a conservative configuration (temperature = 0.1) designed to prioritize consistency and clinical reliability by producing more deterministic responses, and a rather liberal configuration (temperature = 0.8). In the NLP literature the effects of temperature are well represented but systematic clinical applications have yet to be done to our knowledge. Accuracy in multiple choice question answering tasks show high consistency in temperature ranging between 0 and 1, but an expansion to other problem types is recommended (59). This strategic selection of hyperparameters reflects the clinical tension between reproducibility critical for diagnostic applications where consistency across assessments is paramount and the risk of highly inconsistent outcomes that could potentially lead to incorrect diagnoses and treatment recommendations. In addition, we apply top-p (nucleus) sampling with a cumulative probability threshold of 0.9 to each analysis. This setting restricts sampling to the smallest set of tokens whose cumulative probability mass is at least 0.9, balancing output diversity with coherence.

This yields a 2 × 2 factorial design with four experimental conditions: 1. GPT-OSS-120B with temperature 0.1, 2. GPT-OSS-120B with temperature 0.8, 3. GPT-OSS-20B with temperature 0.1, and 4. GPT-OSS-20B with temperature 0.8. We will evaluate each condition's performance on primary outcomes including general diagnostic classification accuracy and suicidality detection, severity score prediction (correlation with standardized clinical measures), and clinical utility metrics such as sensitivity, specificity, and positive/negative predictive values. All model versions, hyperparameters, and inference code will be fully documented and made available to ensure complete reproducibility.

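### Tier 2 takes the model's own predicted score as its response, so the size-by-temperature tests detect shifts in mean score, not differences in accuracy; Tier 1's response is ambiguous on the same point.

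*Protocol article*

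**What the plan says.** All quotes come from the protocol article, under Statistical methods for primary and secondary outcomes.

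- **Purpose.** The comparison of the two model sizes asks "whether larger, more capable models provide sufficient performance advantages to justify their greater computational demands". The alternative that it sets against this is "whether smaller, more efficient models can achieve comparable diagnostic accuracy".
- **Tier 2.** "we will model primary outcome (e.g., predicted depression severity) as a function of fixed effects for model size", together with temperature and the interaction, and with participant and session as random effects. Of a significant interaction the article says "it would suggest that clinical deployment requires model-specific tuning". If there is none, it would give the same advice for both sizes.
- **Tier 1, text.** The aim is "We will analyze each modality independently to establish baseline predictive performance before considering fusion". The model is a "two-way mixed-effects logistic regression with outcomes (diagnostic classification or severity degree) regressed on the fixed effects of model size and temperature".
- **Measures per condition.** Before the tiers, the article says "We will evaluate each condition's performance on primary outcomes including general diagnostic classification accuracy and suicidality detection". It adds correlation with clinical measures, sensitivity, specificity and predictive values.
- **Cell contrasts.** The paragraph on statistical rigor words the contrasts between cells as tests of whether one configuration performs better than another. It does not say on which measure.

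**The concern.** The question is about accuracy, but the one response that Tier 2 names is the language model's output. The reference rating is neither part of that response nor a covariate. Under this model a size or temperature effect means only that one configuration gives higher scores than the other.

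Errors can follow in both directions. A configuration whose scores are far noisier, but right on average, shows no effect. A configuration that removes a systematic bias shows a significant effect, and nothing in the model says which of the two is closer to the truth. Advice on which model size suits a clinical workstation, and on whether temperature must be tuned for each model, would then rest on a test that does not address it.

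**Working it through.** **What the Tier 2 contrast estimates.** The article gives no figure for this point, so the algebra comes first. For session i and configuration c, write

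prediction(i,c) = truth(i) + b(c) + e(i,c), where e has mean 0 and SD s(c).

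All four configurations score the same session, so truth(i) cancels from every within-session contrast:

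- size effect at a fixed temperature = b(120B) − b(20B);
- interaction = the difference between two such bias differences.

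The error SDs s(c) do not appear, whatever their values. Mean absolute error (MAE) depends on both b and s. With b = 0 it is s × √(2/π) = 0.798 s. A difference in s would show in Tier 2 only as unequal residual variance, which the article treats as an assumption violation to be transformed or handled robustly.

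**Illustration.** The 162 sessions come from the Sample size section. That figure reproduces: an exact two-sided binomial test of 0.5 against 0.61, rejecting at 68 or fewer or 94 or more, has alpha 0.04917 and power 0.80468. The rest is assumed, because the article gives no score variances: true score SD 8, one session per participant, four configurations, 500 runs. The size effect was tested within session, averaged over temperature, which in this balanced layout is the main effect.

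*Scenario A: same mean prediction, different accuracy.* b = 0 throughout; s = 2 for 120B and 8 for 20B.
- MAE: 0.798 × 2 = 1.6 and 0.798 × 8 = 6.4.
- Correlation with the truth: 8/√(64+4) = 0.97 and 8/√(64+64) = 0.71 (simulated 0.70).
- Expected size effect on the predicted score: 0 − 0 = 0.

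*Scenario B: same accuracy, different mean prediction.* b = +3 for 120B and −3 for 20B; s = 4 throughout.
- MAE (simulated): 4.05 and 4.04.
- Expected size effect on the predicted score: 3 − (−3) = 6.

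| Scenario | Accuracy differs? | Significant, predicted score as response | Significant, absolute error as response |
|---|---|---|---|
| A | Yes, fourfold in MAE | 5.4% | 100% |
| B | No | 100% | 4.2% |

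The 5.4% and 4.2% are the nominal 5% within simulation error: √(0.05 × 0.95/500) = about 1 percentage point.

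**Tier 1.** The wording allows three readings of the response.

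1. *Correct versus incorrect against the reference.* The odds ratios then compare accuracy, and the model answers its question.
2. *The class that the model predicts.* Then P(predicted positive) = prevalence × sensitivity + (1 − prevalence) × (1 − specificity). At an assumed prevalence of 50%, sensitivity = specificity = 0.95 gives 0.475 + 0.025 = 0.50, and 0.70 gives 0.35 + 0.15 = 0.50. The marginal odds ratio is 1, while accuracy is 0.95 against 0.70.
3. *The clinical label.* It is the same in all four rows of a session, so the odds ratios for size and temperature carry no information.

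**The case against.** The best reply is that the article plainly intends to measure performance. It lists accuracy, correlation, sensitivity, specificity and predictive values for each condition. Its Outcomes section compares model and physician by intraclass correlation or t-test. Tier 3 compares fusion with the best single modality on AUC, sensitivity and specificity. Predicted depression severity is only given as an example, and a condensed article may leave details to an analysis plan that is not shown.

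Much of this stands, and it rules out three stronger readings that a reader might infer.

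- *That the plan as a whole cannot show which configuration is more accurate.* The listed measures would show this descriptively. The size comparison is also called primary in its own right; that label is not attached to the Tier 2 ANOVA.
- *That Tier 1 is wrong as written.* Given its stated aim of predictive performance, correct versus incorrect is a natural reading. The fault is ambiguity.
- *That logistic regression cannot handle several diagnoses or graded severity.* Ordinal or multinomial coding is a detail that an article may leave out.

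The reply does not rescue Tier 2. The example is the only response named there, and any other raw prediction would fail in the same way. This is a response that is stated and does not fit the question, not a missing detail. Nowhere are the listed measures made the response of the factorial tests. The illustration uses contrasts chosen to be clear, so it shows the principle and not the likely effect in this study.

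**Conclusion.** The point holds for Tier 2. As written, the main effects and the interaction test differences in mean predicted score and cannot support conclusions about accuracy, deployment or tuning. This follows from the algebra and depends on no assumed value. The rejection rates (5.4% against 100%, and 100% against 4.2%) do depend on the assumed biases and SDs, and they show that the test can err in both directions. For Tier 1 the finding is limited to an undefined response, with one reading that works and two that do not. The descriptive comparison of accuracy per condition is unaffected.

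**What to change.** **Tier 2.** Make the response the absolute or squared error between the predicted score and a named reference on the same scale, and keep the fixed and random effects as they are. Possible pairs are predicted and recorded BDI-II, or predicted and expert-rated BPRS or CGI-SS severity. The reference has to be named because Data management gives the gold-standard role to an expert rating of the recordings, while the Discussion treats the structured data as ground truth. Report signed error separately as bias. Absolute error is skewed, so apply the transformation or robust variance estimation that the article already allows.

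**Tier 1.** State that the response is a 0/1 indicator, for each session and condition, that the model's classification matches the reference.

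**Cell contrasts.** Say that better performance is judged on these same responses.

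**Cost.** Wording and minor analysis work only. The reference ratings are already planned and no new data are needed. The change should be made before model outputs are analysed.

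### Tier 2 tests model size, temperature and their interaction against one pooled within-session error, so a main-effect test can be anti-conservative and the interaction test underpowered

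*Protocol article*

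**What the plan says.** All of this is in the Protocol article, section Statistical methods for primary and secondary outcomes.

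- **Design.** "This yields a 2 × 2 factorial design with four experimental conditions": two GPT-OSS model sizes by two temperatures. Tier 3 confirms that each condition yields its own output: "For each of the four 2 × 2 factorial conditions, we will generate separate predictions from the GPT-OSS models".
- **Tier 2.** The plan is "using mixed-effects ANOVA to partition variance according to main effects (model size, temperature) and their interaction". It then gives the model: three fixed effects, "with random intercepts for participants and sessions to account for the hierarchical data structure". No term lets the effect of size or temperature differ by session or participant.
- **Tier 1 text model.** The logistic model has the same structure: outcomes "regressed on the fixed effects of model size and temperature, with random intercepts for participant and session".
- **Use of the results.** On model size: "This comparison directly addresses a critical question for clinical deployment". On the interaction: "absence of interaction would support unified recommendations applicable regardless of computational constraints".
- **Testing and checks.** The three fixed effects are tested two-sided at 0.05, with Bonferroni correction within each outcome domain. Robust variance or a transformation is offered if the Shapiro–Wilk or Levene check fails.

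**The concern.** Size and temperature are settings of the software, so all four conditions are naturally run on the same transcript and both factors are crossed within session. A random intercept shifts all four scores of a session equally and drops out of every within-session contrast. What remains is a single residual that serves as the error for all three terms.

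That is right only if the size effect and the temperature effect are each constant across sessions and participants. Two networks may well disagree systematically on particular transcripts, and the plan neither assumes nor tests that they do not. If they do, the pooled residual is too small for one or both main effects and too large for the interaction. A false claim about the primary comparison then becomes more likely. So does a non-significant interaction, which the plan would read as a substantive result.

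**Working it through.** **Plan's own figure.** The article states no error rate or power for Tier 2. Its one design calculation (section Sample size) can be reproduced: an exact two-sided binomial test of 0.5 against 0.61 at N = 162 gives critical values 68 and 94, alpha 0.0492 and power 0.8047. It concerns a different test and does not bear on this point.

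**Inputs from the article.** Four conditions; intercepts only; two-sided 0.05; 162 sessions required and about 200 planned; up to five sessions per participant (section Participant timeline).

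**Assumptions.** One run per cell, since no replicate runs are stated; a balanced continuous response; residual variance 1; session-by-size variance *a* and session-by-temperature variance *b*, both as ratios to the residual. The article gives neither ratio.

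**Expected mean squares.**
- Correct error for size: 1 + 2a
- Correct error for temperature: 1 + 2b
- Correct error for interaction: 1
- Error the Tier 2 model uses for all three: 1 + (2/3)(a + b)

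The correct errors add to 3 + 2(a + b), which is three times the error used. The three ratios R of correct to used error therefore always sum to 3. If *a* or *b* exceeds zero, the interaction ratio is below 1 and at least one main-effect ratio is above 1. Size is the inflated test when 1 + 2a > 1 + (2/3)(a + b), that is, when a > b/2.

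**Type I error.** Large-sample rejection rate under the null = 2·[1 − Φ(1.96/√R)].
- a = 0.25, b = 0: R = 1.5/1.1667 = 1.286, rate 0.084.
- a = b = 1: R = 3/2.3333 = 1.286, rate 0.084 for size and for temperature.
- a = 1, b = 0: R = 3/1.6667 = 1.8, rate 0.144.
- a very large, b = 0: R → 3, rate 0.258.

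**Interaction power**, for an effect that its own error would detect with 80% power: 1 − Φ(1.96/√R − 2.80). At a = 1, b = 0, R = 1/1.6667 = 0.6, and power = 1 − Φ(2.53 − 2.80) = 0.607.

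| a | b | size test | temperature test | interaction test | interaction power |
|---|---|---|---|---|---|
| 0 | 0 | 0.050 | 0.050 | 0.050 | 0.800 |
| 0.25 | 0 | 0.084 | 0.034 | 0.034 | 0.753 |
| 0.5 | 0 | 0.110 | 0.024 | 0.024 | 0.705 |
| 1 | 0 | 0.144 | 0.011 | 0.011 | 0.607 |
| 1 | 0.25 | 0.126 | 0.030 | 0.008 | 0.559 |
| 1 | 1 | 0.084 | 0.084 | 0.003 | 0.424 |
| 2 | 0 | 0.181 | 0.003 | 0.003 | 0.424 |

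**Checks by simulation** (10,000 runs per setting). At a = 1, b = 0 the size test rejected 0.145, and interaction power was 0.60 against 0.79 with its own error. In one simulated data set with a pooled residual of 1.671, a REML fit with the planned intercepts gave the same standard error, 0.0914, for size and temperature. The matching errors gave 0.1255 and 0.0707.

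**Participant-level variation** (40 participants × 5 sessions, b = 0). Splitting the size-effect variance into participant + session parts of 0.1 + 0.4, 0.25 + 0.25 and 0.5 + 0.5 gave size rejection rates of 0.173, 0.257 and 0.345. A session-level error alone still rejected 0.097, 0.161 and 0.199. A participant-level error gave 0.050, 0.047 and 0.051.

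**Bonferroni.** At 0.05/3 with a = 1, b = 0, the size test rejects 0.074, about 4.5 times its nominal level.

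**The case against.** - **No variances are given.** This stands. A reader might infer that the model-size test rejects about three times too often. That is one point, 0.144/0.05 = 2.9, and needs session-by-size variance near the residual with almost no session-by-temperature variance. The documents neither support nor exclude it.
- **Which main effect is inflated is not settled.** A reader might take "Accuracy in multiple choice question answering tasks show high consistency in temperature ranging between 0 and 1" to mean that temperature is harmless and model size must be the inflated test. The remark concerns multiple-choice accuracy, and the same sentence recommends extension to other problem types. Stable average accuracy also says little about session-by-temperature variance. The article itself describes temperature as controlling output randomness; extra noise at 0.8 would raise the residual and shrink the ratio *a*. Only the condition a > b/2 can be stated.
- **The assumption checks may trigger robust variance.** This is partly right. In simulations with assumed variances (162 sessions, 41 participants, 1,000 runs), Levene's test failed in 81–85% of runs when residual variance differed markedly by temperature (a = 1, b = 0). Shapiro–Wilk failed in 72% when scores were rounded to a 1–7 scale. Participant-clustered variance then gave 4–7%. But the plan does not say that its robust variance is clustered, and it also allows a transformation. With equal residuals and continuous scores the checks failed in only 6%. Neither check targets correlated errors within a session.
- **The article is condensed.** An analysis plan could add random slopes. However, Tier 2 spells out its random effects as the specific model, so this is a stated choice and not an omission.
- **Tier 1 is weaker.** The mean-square algebra does not carry over to the logistic model. A conditional-logit stand-in (500 runs) rejected 0.046, 0.058, 0.150 and 0.142 at size-by-session SDs of 0, 1, 2 and 3 on the logit scale, so inflation appeared only under large heterogeneity.

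**Conclusion.** The point holds for Tier 2 in conditional form. With intercepts only and both factors crossed within session, one residual serves three terms that need different errors. If size or temperature effects vary by session or participant, the interaction test is conservative and at least one main-effect test is anti-conservative. This direction needs no assumed variance, but it assumes one run per cell and no separate participant-level variation in the interaction itself.

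The size depends on ratios the article does not give. For model size with session-level variation, the rate is 5% with no heterogeneity, 8% at a ratio of 0.25 (or both ratios 1), 14% at a size ratio of 1 with none for temperature, and about 26% at the limit. It is higher if size effects also vary by participant, and model size is not inflated if session-by-temperature variance is at least twice session-by-size variance. In the 14% case, interaction power drops from 80% to about 60%. Intervals for effects and for partial eta-squared inherit the wrong error. For Tier 1 the case supports a precaution only.

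**What to change.** **Tier 2.** Compute the size, temperature and interaction contrasts once per session, and test the mean of each with participant-clustered standard errors. Name this as the single pre-specified analysis, not as a fallback. An equivalent model with size and temperature random effects by session and by participant would also do, but it is heavier to fit with one run per cell. Derive partial eta-squared and its interval from the error that matches each term.

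**Tier 1 text model.** Use participant-clustered robust variance by default, not only after a failed Shapiro–Wilk or Levene check.

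**Cost.** A few sentences of analysis wording and no new data. Where a main-effect test is now anti-conservative, its interval becomes wider. With 162 sessions, error degrees of freedom fall from 3 × 161 = 483 to 161 or fewer. In simulations of the continuous case, per-session contrasts with participant-clustered errors rejected 4.4–5.6% at nominal 5%.
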